**WP** **III: develop and test an intervention to strengthen** **PCL** **in** **RCFs** **for older people**													
	RQ 10—Which intervention components are relevant and can be adopted in a Swedish aged care context?	✓						✓				✓	
	RQ 11—Are the intervention components feasible, and how are they experienced by the leaders?	✓			✓					✓			
	RQ 12—What are the strengths and challenges of the different parts of the intervention?	✓			✓					✓			
**WP IV: implement and investigate the effects of an intervention to strengthen PCL in RCFs**													
	RQ 13—What are the effects of the intervention?	✓		✓			✓						✓
**WP** **V: generate knowledge about the process of development and implementation of the intervention**													
	RQ 14—How do the participants experience the process of cocreation of the development and implementation of the intervention?	✓			✓		✓			✓			

^a^WP: work package.

^b^RQ: research question.

^c^FLM: first-line manager.

^d^RN: registered nurse.

^e^PCC: person-centered care.

^f^RCF: residential care facility.

^g^PCL: person-centered leadership.

^h^ACLQF: aged care clinical leadership qualities framework.

### Studies With a Qualitative Approach

The qualitative studies concern leaders’ understanding of PCC in RCFs (RQ 1), ethical challenges in the provision of PCC during the COVID-19 pandemic (RQ 2), the meaning of PCL in RCFs from the perspective of leaders (RQ 3), the evidence base of PCL (RQ 5), the feasibility and experience of the intervention components (RQ 11), strengths and challenges of the different parts of the intervention (RQ 12), and the experience of the cocreation process of development and implementation of the intervention (RQ 14).

#### Samples

The sample for the qualitative studies will be purposively selected to include people who can report relevant experiences and describe the phenomenon being investigated [56]. First, permission from the heads of social services representing municipalities of varying sizes in both rural and urban areas in southern, western, and northern Sweden will be collected. Thereafter, first-line managers, RNs, and direct care staff working in RCFs will be invited to participate in the study. They will receive oral and written information about the study at workplace meetings. Interested persons will be asked to contact a member of the research team. The estimated sample size will range between approximately 15 and 20 participants in each group; to ensure variation in experiences, participants will be drawn from different regions of Sweden, diverse workplaces, and will vary in age and work experience [57].

#### Data Collection

Individual and focus group interviews will be performed with leaders and direct care staff. Before data collection, pilot interviews will be conducted to test the interview guide and format. Before the interview, the participants will be asked to provide demographic information. Both the individual and the focus group interviews will be guided by a semistructured interview guide. The focus groups will be relatively small (3-5 participants) to enable digital focus group interviews. Focus group interviews will be conducted by a moderator and an observer. The moderator will facilitate the discussion and ensure that all participants are involved, and the observer will take notes and ask complementary questions [58]. All interviews will be audio recorded, transcribed verbatim, and pseudonymized. The interview guides are in Swedish and are available on request.

For the metasynthesis, data will be extracted from empirical studies retrieved from relevant databases. The review (RQ 5) for establishing the evidence base will be conducted by searches across relevant databases for studies on PCL published in English or a Scandinavian language within the past 20 years, ensuring both relevance and accessibility. Abstracts will be systematically reviewed to assess their alignment with the study’s objectives. Articles that pass this stage will then undergo a quality assessment, following the established guidelines outlined by the Swedish Agency for Health Technology Assessment and Assessment of Social Services [59]. Only studies demonstrating high methodological quality will be included in the analysis.

#### Analyses

The interview material concerning leaders’ understanding of PCC (RQ 1) will be analyzed using a *discourse analytic approach* with a focus on the question “How do leaders talk about PCC?” The analysis will be guided by constructing discourses on PCC to articulate its various aspects and categorize language use regarding specific ways of talking about PCC [60].

The interview material concerning leaders’ experiences of ethical challenges during the COVID-19 pandemic (RQ 2) and the meaning of PCL from the perspective of leaders (RQ 3) will be analyzed using *conventional content analysis,* as described by Hsieh and Shannon [61]. The content analysis will be conducted in several steps: (1) an initial reading of the texts; (2) repeated reading of the transcripts, highlighting text (meaning units) related to the aim; (3) a line-by-line coding of meaning units; (4) grouping of the codes into meaningful clusters; and (5) sorting the clusters by content, grouping content into subcategories, and abstracting to main categories. The analysis will be conducted as a constant iteration between the text, codes, clusters, and possible categories.

The interview material concerning staff experience of ethical challenges in the provision of PCC during the COVID-19 pandemic (RQ 2) and the experience of the cocreation of development and implementation of the intervention (RQ 14) will be analyzed using *thematic analysis*, as described by Braun and Clarke [62]: (1) familiarizing with the data, including multiple readings of the transcripts and a shared discussion of all authors’ initial understanding of the data; (2) coding; (3) sorting the codes into preliminary themes; (4) reviewing and validating the themes in relation to the data; (5) compiling an overview (similar to a thematic map) as a basis for defining and naming the themes; and (6) writing a report [62].

The *metasynthesis* (RQ 5) of the included studies from the database search will be analyzed and synthesized into common themes, covering the content of PCL in existing research. This comprehensive approach will allow for the integration of both theoretical perspectives and empirical evidence. The extracted data will be systematically organized into codes and categories to identify recurring themes, patterns, and variations. Codes and categories will be synthesized into overarching themes that connect the findings to a broader theoretical framework [63]. This will result in a comprehensive compilation of existing evidence regarding PCL.

### Studies With a Mixed Methods Approach

The mixed methods studies will use group concept mapping (GCM) to explore the conceptualization of PCL in RCFs from the perspective of RCF leaders (RQ4) and to refine the intervention components (RQ10).

#### Samples

The sample for the mixed methods studies will likewise be purposively selected to include participants with relevant experience [56]. After permission from the heads of municipal social services has been obtained, RNs (RQ 4) and first-line managers (RQ 4 and RQ 10) will be invited to participate. They will be informed about the study and get in touch with the research team if interested, as is the case with the qualitative studies. The minimum sample size for a GCM study is 20 participants, although a larger sample of 25 to 40 is often used to achieve a more robust result. The sample size for the GCM studies ranges from 30 to 40 [64].

#### Data Collection and Analyses

Data will be collected and analyzed using GCM. This is a collaborative process that combines qualitative and quantitative data collection and analysis with a specific focus. In RQ 4, the characteristics of PCL are the focus, while the focus of RQ 10 is the identification of intervention components. GCM is a structured method for organizing and “mapping” ideas, needs, and preferences [65]. It involves the following steps: (1) brainstorming with participants using a prompt; (2) organizing the responses (where additional aspects from RQ 3 will be added for RQ 10, if missing) and entering them into the program Groupwisdom (Concept Systems Inc); (3) participants rate the responses in relation to how important and how feasible the response is on a 4-point scale where 1=“not at all” and 4=“very much”; (4) analyzing the responses based on their relationships (qualitative analysis) and ranking (basis for quantitative analysis); (5) conducting quantitative analysis of the organization and ranking in the Groupwisdom program, resulting in ≥1 visual figures; and (6) interpreting the visual figures together with the participants [66].

### Studies With a Quantitative Approach

The studies with a quantitative approach involve the translation and cultural adaptation of the ACLQF (RQ 6); development of an instrument to measure PCL (RQ 7); identification of other relevant outcome measures concerning staff, leaders, and care quality (RQ 8); and identification of health economic outcome measures and economic considerations (RQ 9). The quantitative studies will have correlational (RQ 6 and 7) and descriptive (RQ 8 and 9) designs.

#### Samples

The sample for the studies with correlational designs will be composed of RNs (RQ 6), first-line managers (RQ 6 and 7), and direct care staff (RQ 7). The estimated sample size for RQ 6 is 30 participants (15 RNs and 15 first-line managers), as the preferred range for calculation of item-level content validity index (I-CVI) is approximately 10 experts from each group [67]. The estimated sample size for RQ 7 is 40 first-line managers participating in the development of the scale and approximately 100 direct care staff for the evaluation of its psychometric properties. The sample size of 100 is preliminary, as it depends on the number of items in the scale and needs to be adequate for the calculation of both internal consistency and test-retest reliability, as well as for exploratory factor analysis [68]. The studies with a descriptive design will be based on literature searches (RQs 8 and 9).

#### Data Collection and Analyses

The framework will initially be translated into Swedish using forward and backward translation (English-Swedish-English) by 2 independent translators. Thereafter, the participants will be asked to complete a web survey in which they will rate the relevance of the 40 translated statements in the framework on a 5-point scale, ranging from 1=“not at all relevant in a Swedish context” to 5=“to a high degree relevant in a Swedish context.” The test of the prefinal version, the cultural validation, will be examined using the I-CVI, where the number of participants giving the rating “relevant” (3 or 4) for each item will be divided by the total number of participants. When all participants rate an item as relevant, the I-CVI is 1.0. As recommended by Polit et al [67], a scale can be judged as having excellent content validity if the items have an I-CVI of ≥0.78. The cultural adaptation of the ACLQF has already been finalized and published (refer to the Results section).

The development of an instrument to measure PCL in RCFs from the perspective of staff, the PCL Questionnaire, will follow the Consensus-Based Standards for the Selection of Health Measurement Instruments (COSMIN) guidelines [69]. The development will be conducted in four phases: (1) deriving items based on the results from RQ 5, (2) preliminary testing, (3) analysis, and (4) psychometric evaluation [68]. The developed instrument will be used as the primary outcome measure when investigating intervention effects.

In the first phase, relevant statements (items) will be developed through the following steps: (1) formulation of specific items, where statements are carefully crafted to be clear, concise, and easy to understand; (2) face validity testing through cognitive interviews with managers and staff to evaluate the comprehensibility and interpretability of the items and to identify potential issues; and (3) revisions based on feedback, where items are revised for clarity and precision according to the feedback obtained during the interviews.

In the second phase, preliminary testing of the instrument will be conducted using classical test theory to identify and minimize measurement errors. Classical test theory will also be used to reduce the number of items and thus optimize the instrument’s efficiency. In the third phase, a 2-parameter item response theory model will be applied to gain a detailed understanding of how individual items function regarding difficulty and discrimination. This model addresses how well each item differentiates between participants with varying degrees of the ability in focus (ie, varying degrees of PCL). In the fourth phase, psychometric evaluations will be conducted to ensure the instrument’s reliability and validity. This fourth step will also include a test-retest assessment to examine the instrument’s stability over time, as well as refinement and adjustments to the instrument following the results of the psychometric evaluations. The instrument will be freely available for research purposes and academic use. Commercial exploitation and use in business activities will not be permitted without prior written approval from the authors.

Relevant outcome measures concerning leaders, staff, care quality, and economic measures (RQs 8 and 9) will be identified through a systematic search of the literature, where instruments showing reliable and valid psychometric properties will be selected. The identified instruments will be discussed in the steering group and the reference group regarding quality, feasibility, and the possibility of detecting intervention effects. These instruments will be used as secondary outcome measures when investigating intervention effects.

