### Translation and Cultural Adaptation of the ACLQF

The ACLQF was translated into Swedish, cross-culturally adapted, and validated. It was shown to be useful and suitable for leaders in residential care in Sweden. The framework clarifies the leader’s role and identifies leadership attributes and requirements for PCL in residential care, thereby providing support to leaders by framing PCL [74].

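### The I-CVI rule for RQ 6 counts only ratings of 3 or 4 as relevant on a scale described as 1 to 5, so the highest rating counts against a statement; the scale or the cut-off is misstated

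*Protocol article*

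**What the plan says.** In the protocol article, Methods, Studies With a Quantitative Approach, Data Collection and Analyses, participants in RQ 6 are asked to "rate the relevance of the 40 translated statements in the framework on a 5-point scale". The lowest point, 1, is labelled "not at all relevant in a Swedish context" and the highest, 5, is labelled "to a high degree relevant in a Swedish context". Points 2, 3 and 4 carry no label.

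The same paragraph defines the I-CVI. The number of participants who rate an item as relevant, identified as "3 or 4) for each item will be divided by the total number of participants", gives the index. It adds: "When all participants rate an item as relevant, the I-CVI is 1.0". The benchmark is that "a scale can be judged as having excellent content validity if the items have an I-CVI of ≥0.78".

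The Samples section gives the planned number of raters: "The estimated sample size for RQ 6 is 30 participants (15 RNs and 15 first-line managers").

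The adaptation is described as finished and published. Of the framework, the Results section reports: "It was shown to be useful and suitable for leaders in residential care in Sweden".

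**The concern.** The scale and the set of ratings that count as relevant do not fit each other. On a scale that ends at 5, a rule that counts 3 and 4 leaves out the most favourable answer. A 3-or-4 rule takes in the top of the scale only if the scale has four points. The only 4-point scale in the article is the group concept mapping rating for RQs 4 and 10, which is a different exercise. Nothing says that 5 is also counted, that categories were merged, or that this survey used four points.

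The I-CVI against 0.78 is the only criterion given for judging the ratings in RQ 6. A reader cannot tell which rule lies behind the reported suitability of the framework, and anyone repeating the method from this text would score the best-endorsed statements lowest.

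**Working it through.** **Inputs.** Scale 1 to 5, relevant set {3, 4} and benchmark 0.78, all from Data Collection and Analyses. Planned raters n = 30, from Samples.

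**Formula.** I-CVI = (number of ratings in the relevant set) / n.

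**The article's own figure.** If all 30 ratings fall in the relevant set, I-CVI = 30/30 = 1.0. This agrees with the text.

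**Ratings needed.** 0.78 × 30 = 23.4, so 24 are needed: 24/30 = 0.800 meets the benchmark and 23/30 = 0.767 does not.

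**Tolerance for top ratings.** Under {3, 4}, each rating of 5 is lost from the numerator. At most 30 − 24 = 6 can be tolerated, even if every other rater gives 3 or 4. For any number of raters, a statement falls short once more than 1 − 0.78 = 22% choose 5.

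**Constructed examples, n = 30.**

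| Ratings given | {3, 4} as written | {4, 5} | {3, 4, 5} |
|---|---|---|---|
| 30 × 5 | 0.000 | 1.000 | 1.000 |
| 23 × 4, 7 × 5 | 0.767 | 1.000 | 1.000 |
| 24 × 4, 6 × 5 | 0.800 | 1.000 | 1.000 |
| 2 × 3, 8 × 4, 20 × 5 | 0.333 | 0.933 | 1.000 |
| 2 × 2, 4 × 3, 10 × 4, 14 × 5 | 0.467 | 0.800 | 0.933 |
| 30 × 3 | 1.000 | 0.000 | 1.000 |

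**How likely a shortfall is.** The article gives no rating distribution, so the chance that a rater chooses 5 is an assumption, varied over a range. Under {3, 4}, seven or more ratings of 5 guarantee a shortfall:

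| Assumed chance of a 5 | P(at least 7 of 30 choose 5) |
|---|---|
| 0.2 | 0.39 |
| 0.3 | 0.84 |
| 0.4 | 0.98 |
| 0.5 | 0.9993 |

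**Two full assumed distributions over ratings 1 to 5.** The chance of reaching 24 of 30 is binomial, with success probability equal to the sum over the relevant set.

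- Well endorsed (0, 0.02, 0.08, 0.30, 0.60). The sums are 0.38 for {3, 4}, 0.90 for {4, 5} and 0.98 for {3, 4, 5}. The chances of reaching the benchmark are about 0.000, 0.974 and about 1.000.
- Lukewarm (0.05, 0.10, 0.60, 0.20, 0.05). The sums are 0.80, 0.25 and 0.85. The chances are 0.607, about 0.000 and 0.847.

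Leaving out 5 makes well-rated statements fall short against either alternative. The rule as written favours lukewarm statements only by comparison with {4, 5}; against {3, 4, 5} that effect disappears.

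**The case against.** The strongest reply is that this is a slip of description in a completed sub-study. The framework was found suitable. If statements were rated highly on a 1-to-5 scale, the literal rule would have scored them low, so the favourable result gives some reason to doubt that it was applied. That is a fair inference but not proof, because the published report is not at hand. The sentence is wrong either way.

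Several stronger readings are tempting, and the text does not support them:

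- *The rule contradicts the sentence on an index of 1.0.* It does not. Once relevant is defined as 3 or 4, that sentence is true by definition. The zero for thirty ratings of 5 follows from the one mismatch already described.
- *A neutral midpoint is wrongly counted as relevant.* Only the end points are labelled. Calling 3 neutral is a reading, and whether it should count is left open.
- *Good statements would be rejected and weak ones kept.* The 0.78 figure is a benchmark for calling content validity excellent. No rule for dropping or retaining statements is given.
- *The measurement of intervention effects is compromised.* The section The Intervention does say that this measurement will build on RQs 6 to 9, but it gives no route by which the I-CVI enters. The primary outcome is the separate PCL Questionnaire, with items derived from RQ 5 and its own psychometric testing. Secondary measures come from literature searches. The framework is nowhere named as an outcome measure.

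**Conclusion.** The point holds as an internal inconsistency: a scale that ends at 5 is paired with a relevant set that stops at 4. Omitting 5 is the clear error and needs no view on what 3 means. Taken literally with 30 raters, seven ratings of 5 are enough to put a statement below 0.78.

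The count of seven assumes that all 30 planned raters responded and were pooled; the article calls 30 an estimate. The 22% limit does not depend on that number. The probabilities rest on assumed rating distributions and show what could happen. A reader might infer that the reported suitability of the framework is wrong. The article does not support that, because it does not show which rule was applied.

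Severity is moderate to minor. RQ 6 is preparatory, and its effect on the later intervention study is indirect.

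**What to change.** Check the survey form and the analysis actually used for RQ 6, then correct the paragraph in Data Collection and Analyses.

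- If the scale was 1 to 4, correct the stated scale length and the value attached to the top label, and keep 3 or 4.
- If the scale was 1 to 5, correct the relevant set so that it includes 5, and state whether 3 was counted. The article does not favour 4-5 over 3-5, so the correction should report what was done and not choose a cut-off afterwards.
- If 3 or 4 was literally applied to 1-to-5 ratings, re-tabulate the I-CVI for all 40 statements against 0.78, using the actual number of respondents. Show the 4-5 and 3-5 results side by side.

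In the first two cases the cost is a short text correction. In the third it is a few hours of re-tabulation from the existing ratings, and some statements may change status against the benchmark.

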### The Intervention

The insights gained from the earlier WPs (WP I-III; Figure 1) will guide the development of the intervention content, structure, and evaluation methods. A cluster randomized quasi-experimental study will be conducted, focusing on PCL through a complex intervention specifically tailored to support first-line managers in the care of older people. This design will ensure that the intervention is evidence based, relevant, practical, and user-friendly, addressing the unique challenges of—and opportunities within—the aged care context. By systematically incorporating knowledge from the earlier phases, the intervention aims to create a well-considered approach to strengthen PCL practices and gradually impact PCC quality. During the initial phases, the program theory will undergo further refinement. The tentative conceptualization posits that by supporting the leaders in practicing PCL, the implementation and overall quality of PCC will increase. This improvement is expected to positively affect the staff’s working environment, working conditions, and work satisfaction, ultimately contributing to the well-being of residents.

As the intervention concerns leaders, an appropriate cluster would be the unit for which each leader is responsible. However, additional information derived from WP III is needed to understand how different units are connected, to estimate the risk of contamination and determine which units should be included in the randomization.

The measurement of intervention effects (RQ 13) will be based on the results from RQs 6 to 9, while the sample will be composed of first-line managers and direct care staff. The sample size will be determined by power analyses based on expected differences in primary and secondary outcome measures.

### Timeline

Some studies in WP I started already in 2022 and will be concluded by 2026. WP II will run between 2026 and 2027, WP III will run through 2028, and WP IV is planned to start in 2029. Finally, WP V will run in parallel with WP III and IV (Figure 2).

